### Participants

#### Eligibility Assessment

 The study will be conducted in adults diagnosed with CPSP who attend the Neurology Service, Pain Unit, and/or the Rehabilitation Service at the ULS-Coimbra, Portugal. Inclusion criteria include (1) medical diagnosis of CPSP conducted by a medical doctor collaborating with the research team, (2) age between 18 and 80 years, (3) implicit de facto internet and computer literacy, and (4) willingness to comply with the study procedures. Exclusion criteria include (1) currently with active malignancy, (2) severe cognitive impairment, (3) currently undergoing any psychological intervention or VR-delivered pain management program, (4) current severe psychiatric symptoms (ie, psychosis, severe depression, nonsuicidal self-injury, suicide attempt in the last month), (5) language impairment with severe comprehension deficit, (6) history of photosensitive epilepsy or previous experience of severe simulator sickness, and (7) other neurological conditions (eg, dementia or Parkinson disease).

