#### Sample Size Calculation

 The study was powered for a large final timepoint between-group effect size (standardized mean difference=0.8), allowing for a variant autoregressive ρ over 2 measurements (preintervention and postintervention; 1 and 0.8) to accommodate the likely instability of the outcome variable(s). Setting the α at .05 and a minimum of 80% power, a minimum sample size of N=30 is required (EC: n=15; CC: n=15). We used the power.mrmm function from the R “longpower” package, through WebPower. A sample size of 15 to 30 participants is also sufficient to attain saturation in qualitative analyses conducted through interviews [32].

 To minimize dropout, (1) 2 phone calls will occur during the VR-ACT implementation to address questions on the VR-ACT content. (2) We also expect minor technical difficulties when using the VR headset. At the beginning of each module, an avatar therapist will provide a welcome message, reminding you of the research team’s contact information in case of any technical problems. Before the implementation, an online group meeting will be conducted to introduce the VR headset to participants in both conditions and help with navigation. (3) To promote engagement, weekly emails will be sent to all participants reminding them to use the VR headsets. Also, after the VR system registers 3 days of absence, automatic reminders will be sent to the participants' emails.

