#### Data Collection

The research team members, who are physicians at the Neurology Service, the Pain Unit, and/or the Rehabilitation Unit of ULS-Coimbra, Portugal, will invite participants and inform them of the aims and conditions for participation. Those who provide written informed consent will be screened for medical eligibility. Then, psychological eligibility will be individually assessed, online and at a time preferred by participants, by the clinical psychologists of the research team, for severe neurocognitive and psychiatric symptoms (using Mini Mental State Examination and a semistructured clinical interview adapted from Structured Clinical Interview for DSM). Those who meet criteria for severe psychiatric disorders and/or cognitive impairment will be excluded from the study, given feedback, and advised to seek medical/psychological consultation. Eligible participants will receive the link to the online preintervention assessment (T0) self-report protocol. A task-oriented (see Section B in Multimedia Appendix 1) functional magnetic resonance imaging (fMRI) will be scheduled to collect preintervention data on the functional connectivity of the triple network (DMN, SN, and FPN). Participants will then be randomly assigned by a member of the research team to 1 of 2 conditions (EC and CC) using random permuted blocks to ensure balance in age (via an online randomizer, eg, random.org [35]). Participants will be informed of the starting date via telephone (or alternatively via email). The medical/nursing collaborators and the research team members not involved with the implementation monitoring will be blinded to the allocation. The two conditions will be masked to participants by not explicitly informing whether the content of the VR is 3D (VR-ACT) or 2D (Sham VR), with both being delivered through the same model of VR headset (MetaQuest 3.0). Nevertheless, for ethical reasons, the two conditions in the study are described in the patient information sheet. A scheduled meeting in the ULS-Coimbra will be held to provide headset devices to participants. Three groups or waves of recruitment and VR-ACT implementations will be conducted (group 1, n=10; group 2, n=10; group 3, n=10; see Figure 1). At the end of implementation, participants will return the devices and will conduct the post-intervention assessment (T1): online psychosocial self-report data collection; and functional connectivity of the triple network data collection (fMRI). Additionally, participants in the EC will be interviewed online by a research team member who is blind to the allocation to collect qualitative data on the acceptability and usability of the VR-ACT (see Section A in Multimedia Appendix 1). The time points of measurements are described in the SPIRIT figure (See Figure 2).

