### Data Analyses: Feasibility and Preliminary Efficacy

The feasibility of VR-ACT will be assessed qualitatively through open-ended questions (eg, “What would you say were the benefits of using the VR-ACT headset?,” “What have you learned from the VR-ACT program?”) designed to explore adherence, engagement, and acceptability of the intervention (see Section A in Multimedia Appendix 1). Thematic analyses will be conducted with the support of NVivo, and common themes in each question will be categorized. Also, feasibility will be quantitatively assessed through (1) dropout rate, (2) number of usage of the VR headset (embedded software usage monitoring), (3) percentage of intervention completion, (4) a 5-point Likert scale measuring usefulness, comprehensibility, and likelihood to continue using learned skills. The usability of the VR-ACT will be quantitatively assessed through the System Usability Scale.

The preliminary efficacy of VR-ACT will be pilot tested through 2 statistical methods: (1) intention to treat analyses, using linear mixed models to examine statistically significant change over time, moderated by allocation, and post hoc differences, adjusted for multiple comparisons using the Bonferroni technique; (2) reliable change index for each outcome for preintervention to postintervention timepoints, to assess clinically significant individual changes [48]. Network-based statistics [49] will be used to assess significant differences in network connectivity within and between conditions.

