### Ethical Considerations

All procedures will be conducted in accordance with the 1964 Helsinki Declaration and its subsequent amendments or comparable ethical standards. This study was approved by the Ethics Committee of the Faculty of Psychology and Educational Sciences at the University of Coimbra (ref: CEDI/FPCEUC: 98/R-1). The study will be conducted in accordance with European directives for research involving human participants, such as the General Data Protection Regulation. All participants will provide informed consent to participate in the study. Participants will be provided a patient information sheet with the following information: (1) the aim of the study and the eligibility criteria for participating; (2) the different phases of the study, including assessments and the randomization; (3) the benefits and risks of participating (namely that “We do not anticipate any risks arising from your participation in the study. However, if participating in the study results in a negative emotional experience and you need support, please contact the research team” and other national health resources will be provided). In this case, their participation will be interrupted. (4) Participation is voluntary, participants have the right to drop out without being obligated to provide justification, and access to treatment as usual, as well as their relationships with the medical and nursing team, will not be influenced by this decision; also, the decision to participate will not interfere with their medical treatment; (5) the confidentiality of data will be ensured in all results dissemination activities, and identifiable data in datasets will be password protected, to which only the research team will have access; (6) audio recording of postintervention interviews will be immediately deleted after written transcription. Informed consent will be obtained from each participant by the medical/nursing collaborator who will invite patients to participate before any data collection. (7) The current study will not conduct an assessment of neurological pathology; thus, data collected through fMRI will not be indicative of clinical diagnoses nor associated pathophysiology. The study results will be provided to interested participants in a format that is accessible.

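### Interrupting participation after a negative emotional experience can remove T1 data for a reason tied to a primary outcome; T1 follow-up should be kept separate from VR use

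*Protocol article*

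**What the plan says.** - **Interruption rule (Ethical Considerations).** The information sheet tells participants "if participating in the study results in a negative emotional experience and you need support, please contact the research team". The article then adds: "In this case, their participation will be interrupted". The rule is addressed to all participants, not to one arm. It does not say whether the VR sessions, the assessments or both are interrupted.
- **Timing of assessment (Data Collection; Sample Size Calculation).** There are two measurements, T0 before and T1 after the intervention. T1 takes place at the end of implementation, when the headsets are returned. No separate arrangement is given for someone interrupted earlier.
- **Outcomes (Primary Outcomes).** Psychological distress on the DASS-21 is listed with pain intensity, pain disability and quality of life.
- **Analysis (Data Analyses: Feasibility and Preliminary Efficacy).** The first method is "intention to treat analyses, using linear mixed models to examine statistically significant change over time, moderated by allocation". The second is a reliable change index for each outcome from before to after the intervention.
- **Attrition (Assessment of the VR-ACT Delivery).** Completing the intervention (adherence) and completing the T1 assessment (retention) are counted separately. Neither item says that T1 is sought from people whose participation was interrupted.

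**The concern.** The trigger for interruption is emotional deterioration after randomisation, which is close to what the DASS-21 measures. If interruption also ends data collection, the people most likely to have a poor T1 distress score are the ones without a T1 score, and the plan itself creates that loss.

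A participant without T1 gives the mixed model a baseline value only. The model then in effect predicts T1 from participants with a similar baseline who were not interrupted. That is valid if, given baseline, the loss is unrelated to T1. Here the reason for the loss arises after baseline and is related to T1, and no intermediate measurement carries the information. The reliable change index is affected more directly, because an individual's deterioration cannot be computed without T1. The post-intervention interviews in the experimental arm could miss the same people.

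At stake is a pilot estimate that the Discussion offers as a reference point for a larger multicentre study, and the visibility of individual harm in the T1 outcomes.

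**Working it through.** **Step 1: which reading is more natural?** The sentences leading up to the rule speak of participation in the study as a whole, and the next item of the same list uses the word participation for being in the study voluntarily. That favours the reading that study participation ends. Against it, the article elsewhere separates stopping the intervention from missing T1 (adherence versus retention), and it uses a different term for voluntary withdrawal. Loss of T1 is therefore the likely reading, not a stated fact.

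**Step 2: inputs for the size.** From Sample Size Calculation: 15 per arm and a planned standardised difference of 0.8. These are taken as given. Whether the stated inputs lead to 30 participants is a separate matter with no bearing here. The 0.8 in the article's autoregressive term is read as the T0–T1 correlation, which is an assumption. The article gives no interruption rate, so the number interrupted (1 to 3 of 15) and the size of harm are also assumptions.

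**Step 3: model.** Outcome scaled to SD 1, higher meaning more distress. T0 = x and T1 = 0.8·x + √(1 − 0.8²)·e = 0.8·x + 0.6·e, with x and e independent standard normal and no true treatment effect. The estimate is the arm difference in T1 adjusted for T0, standing in for the mixed model, averaged over 3,000 simulated trials per scenario. Negative values favour VR-ACT.

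**Step 4: the participants with the largest worsening (T1 − T0) are interrupted.**

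| Interrupted in VR-ACT | Interrupted in sham | Mean estimate, their T1 missing | Mean estimate, their T1 collected |
|---|---|---|---|
| 1 | 0 | −0.067 | 0.002 |
| 2 | 0 | −0.130 | −0.005 |
| 3 | 0 | −0.189 | 0.011 |
| 2 | 2 | −0.006 | 0.000 |
| 0 | 2 | +0.135 | 0.003 |

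The true value is 0 in every row. Relative to the planned 0.8, the first and third rows are 0.067/0.8 = 8% and 0.189/0.8 = 24%.

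**Step 5: k VR-ACT participants are truly harmed by 1 SD and interrupted, none in sham.** The true arm difference is k × 1/15, that is 0.067, 0.133 and 0.200 for k = 1, 2 and 3.

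| k | True difference | Mean estimate, T1 collected | Mean estimate, T1 missing |
|---|---|---|---|
| 1 | 0.067 | 0.074 | 0.005 |
| 2 | 0.133 | 0.139 | 0.005 |
| 3 | 0.200 | 0.200 | −0.001 |

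With T1 missing, the harm does not appear in the estimate. With T1 collected, it does. If the harm is 0.5 SD, the estimates with T1 collected are 0.034, 0.072 and 0.099, and those with T1 missing are again about 0.

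**The case against.** **The rule may mean VR use only.** This stands as a possibility. If T1 is collected, the bias in Step 4 disappears to within about 0.01. But a sentence that can be read as ending follow-up will be applied that way by some staff, so it needs limiting even if the intention was narrower.

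**The rule covers both arms.** This stands. A reader might infer that the estimate is biased in favour of VR-ACT; the documents do not support that as a flat statement. Unequal losses are plausible: Textbox 1 includes practice with difficult emotions, whereas the sham arm receives distraction videos, and the distress stopping rule watches only the VR-ACT arm. But no interruption rates are given, and losses in sham would push the other way.

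**The size is small against random error.** With 15 per arm, the standard error of the adjusted difference is about 0.6 × √(2/15) = 0.22 SD, so 0.07 to 0.19 lies within one standard error, and the Discussion already disclaims definitive efficacy conclusions. This stands, and limits the weight of the point. The error is nevertheless systematic and cheap to avoid.

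**Follow-up after stopping and sensitivity analyses may be in a fuller document.** True, and their absence from an article would not be a finding. The point rests on a rule that the article does state.

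**Stronger inferences that fail.**
- That the analysis is not intention to treat: a mixed model can keep baseline-only participants in the arm to which they were allocated. The difficulty is missing data, not the analysis set.
- That the steering committee would not see the harm: it meets during delivery (weeks 1, 3, 6 and 8), its distress rule uses reports after session 1, and interruption follows from contact with the team. None of this depends on T1.
- That the sheet's risk statement, "We do not anticipate any risks arising from your participation in the study", flatly contradicts the protocol: the next sentence of the sheet allows for negative emotional experiences, and excluding people with "history of photosensitive epilepsy or previous experience of severe simulator sickness" lowers those risks among the people enrolled. There is a tension of wording with that exclusion and with the stopping rule, no more.

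**Conclusion.** The point holds in conditional form. The article states an interruption rule triggered by an event closely related to a primary outcome, and nothing in it keeps the interrupted participants in T1. If the rule ends data collection, the loss is outcome-related and a two-timepoint analysis cannot recover it.

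The size depends on assumptions the documents do not supply: a T0–T1 correlation of 0.8, 1 to 3 of 15 interrupted, and those people being the worst changers. If all losses fall in VR-ACT, the bias is about 0.07 to 0.19 SD towards VR-ACT, roughly a twelfth to a quarter of the planned 0.8. It is about 0 with two losses in each arm, and about 0.13 SD against VR-ACT with two losses in sham only. A correction is worth making because it is specific and cheap, not because bias has been shown.

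**What to change.** 1. Leave the clinical decision on interrupting VR use unchanged. State that the interruption applies to VR use, and that the T1 self-report (and fMRI, if the participant is willing) is sought from every randomised participant unless consent to data collection is withdrawn. Analyse everyone as allocated.
2. Report interruptions and their reasons by arm.
3. Add one sensitivity analysis that assigns unfavourable T1 values to interrupted participants whose T1 is still missing.
4. As a secondary matter, reconcile the sheet's risk wording with the simulator-sickness and photosensitive-epilepsy exclusion and with the distress stopping rule.

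**Cost:** one protocol sentence, matching wording in the information sheet through the ethics committee, and one questionnaire for a few people. The T1 self-report is already online, and the Results section says recruitment had not started. The downside is small: some who stop will decline T1, which is what the sensitivity analysis is for.

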**Figure 1. F1:**
[figure not shown]
Flowchart of participants. ACT: acceptance and commitment therapy; CC: control condition; EC: experimental condition; VR: virtual reality.

 During the development of the VR-ACT intervention, a patient and public involvement group will be formed to monitor the adaptation of the exercises into VR and their tailoring for patients with CPSP. The group (n=5) will consist of 1 medical doctor and 1 nurse working in CPSP rehabilitation, 1 clinical psychologist specializing in contextual behavioral approaches to chronic pain, and 2 patients with CPSP (1 male and 1 female). The research team and the patient and public involvement group will gather monthly during the development of the VR-ACT intervention to ensure the patient-centered adaptation of exercises is successful and acceptable.

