A steering committee composed of 1 participant, 1 physician (anesthesiologist), 1 clinical psychologist, and 1 ethicist will monitor the delivery of the 8-week VR-ACT intervention and ensure the ethical and scientific integrity of the study (eg, adherence to the protocol). The steering committee will gather online at weeks 1, 3, 6, and 8 to discuss the trial progress, methodological issues arising from the implementation, and ethical decision-making. The trial will be interrupted if >50% of participants in the VR-ACT condition report increased psychological distress after session 1, and/or if >50% of the members of the steering committee decide so.

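### The steering committee seats one participant, on the plain reading an enrolled person, which conflicts with the participant masking

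*Protocol article*

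**What the plan says.** Ethical Considerations sets out the committee: "A steering committee composed of 1 participant, 1 physician (anesthesiologist), 1 clinical psychologist, and 1 ethicist will monitor the delivery" of the eight-week programme. On its meetings it says: "The steering committee will gather online at weeks 1, 3, 6, and 8 to discuss the trial progress, methodological issues arising from the implementation". Two triggers for interrupting the trial follow, joined by and/or. The first concerns one arm: "The trial will be interrupted if >50% of participants in the VR-ACT condition report increased psychological distress after session 1". The second is a vote: "if >50% of the members of the steering committee decide so".

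The Data Collection section describes the masking: "The two conditions will be masked to participants by not explicitly informing whether the content of the VR is 3D (VR-ACT) or 2D (Sham VR"). The headset model is the same in both arms. The section adds that the information sheet describes both conditions. It also says that the research team members who are blinded to allocation are those not involved in monitoring the implementation.

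The Design section, in the text below Figure 1, describes a separate patient and public involvement group. Its members include "1 clinical psychologist specializing in contextual behavioral approaches to chronic pain, and 2 patients with CPSP (1 male and 1 female").

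The four primary outcomes (pain intensity, pain disability, psychological distress, quality of life) are all self-report scales. Participants rate the VR-ACT modules for acceptability, and VR-ACT usability is measured by the System Usability Scale. Both are feasibility evidence.

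**The concern.** A masked participant is asked to help oversee delivery of one of the two arms. Someone who attends meetings about how VR-ACT is being delivered, what problems have arisen and whether the trial should continue receives information that the masking is meant to withhold. They can compare what they hear with what they see in their own headset and work out their arm. They then complete the self-reported primary outcomes. If their arm is VR-ACT, they also rate the acceptability and usability of a programme that they have been overseeing.

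Two things are at stake. One is expectancy: with self-reported outcomes, knowledge of the arm and a stake in the programme can move the scores. The other is role conflict: the same person would be a source of trial data and a voter on whether the trial continues.

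**Working it through.** No figure in the article is in dispute, so the check is mainly textual. The arithmetic only gives scale.

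**Step 1. Who is meant?** The committee sentence says *1 participant*. In the same paragraph the word is used for people in the VR-ACT condition, that is, randomised people. Where the article means lay advisers, in the Design section, it calls them patients with CPSP. The consistent reading is therefore an enrolled person. The text does not say so outright, and a patient representative may have been intended.

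**Step 2. What would that person hear?** The stated tasks are monitoring VR-ACT delivery and discussing progress and implementation problems. In the research team, the article confines blinding to those who do not monitor implementation, so it already treats monitoring as a role that need not be blind. Nothing says that the participant member is kept from arm-level information.

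**Step 3. When?** Meetings are at weeks 1, 3, 6 and 8, and the post-intervention assessment (T1) comes at the end of implementation. If those weeks are the member's own eight weeks, all four meetings fall before T1. There are three waves of 10. The article does not say which wave the member would come from, and a member from a later wave could hear about earlier waves before finishing treatment.

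**Step 4. How large?** Inputs from Sample Size Calculation: N = 30, 15 per arm, planned standardised mean difference 0.8. Assumption, not in the documents: the unmasked person's score shifts by d = 1 to 2 SD.

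- Share of the sample: 1/30 = 3.3%.
- Share of an arm: 1/15 = 6.7%.
- Shift of the arm mean = d × 1/15. For d = 1 this is 0.07 SD; for d = 2 it is 0.13 SD.
- Relative to 0.8: 0.067/0.8 = 0.08 and 0.133/0.8 = 0.17, so about a twelfth to a sixth of the planned difference.

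The direction is not fixed. An encouraged VR-ACT member or a disappointed sham member would widen the contrast; an encouraged sham member would narrow it.

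**Step 5. Voting power.** More than 50% of 4 members means more than 2, so at least 3 votes. The participant holds 1.

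**The case against.** The strongest reply is that this is loose wording. The article never says *trial participant*; a non-randomised patient representative may be meant, and then masking is untouched. This stands as a possibility, but it leads to the same correction, because the sentence as printed says something else.

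A second reply is that little masking is left to lose. Every participant is told that two conditions exist and what they are, and the Discussion concedes that people may tell them apart. This limits the harm, and it would be wrong to describe an intact mask broken by one seat. It does not remove the point: guessing one's condition differs from attending repeated meetings on how VR-ACT is going.

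Third, a reader might infer that the committee applies the distress trigger and so sees arm-level data, or that the member would certainly learn their arm. The article does not say either. It lists the distress trigger alongside the vote without saying who applies it, and unmasking is a risk inferred from the member's role.

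Fourth, a reader might extend the point to the two patients in the involvement group, who "will gather monthly during the development of the VR-ACT intervention" with the research team. The closest exclusion in Eligibility Assessment covers people "currently undergoing any psychological intervention or VR-delivered pain management program", which does not mention advisers. But no section says that these patients may or will enrol, their eligibility cannot be judged from their sex and diagnosis alone, and a condensed article may leave such a rule to the full protocol. That is at most something to clarify and is not part of this finding. Adding them to reach 3 of 30 is not supported.

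**Conclusion.** The point holds for the committee seat. As written, the article gives one participant, on the plain reading a randomised one, a monitoring and voting role that conflicts with the masking described under Data Collection. It rests on that reading of one word and on the absence of any stated limit on what the member sees.

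The likely effect is modest: one person in an arm of 15, and a movement of 0.07 to 0.13 SD under an assumed individual shift of 1 to 2 SD. In a pilot that disclaims definitive conclusions on efficacy, this would not by itself overturn a result. It also does not mean that one participant could halt the trial, since three of four votes are needed. It is still worth correcting, because it is an avoidable weakening of an already fragile mask, and all the primary outcomes depend on self-report.

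**What to change.** Reword the committee sentence in Ethical Considerations so that the lay member is a person with chronic poststroke pain who is not, and will not be, randomised in this trial. This keeps the patient voice on the committee and reconciles the sentence with the masking text.

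The cost is one sentence and at most one patient lost from the eligible pool. The article reports that recruitment had not started, so at that stage the change affects no data. If an enrolled person has since taken the seat, the report should say so, give that person's arm and the timing of the meetings relative to their T1 assessment, and show the primary outcomes with and without them.
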